### Data management and statistical analysis (sample size)

Due to multiple outcome settings, the OHS was used as the primary outcome measure and power calculations were carried out accordingly. Thus, a sample size of 40 patients per intervention group has been calculated as being sufficient when a 5 point mean difference (SD 7.8 point) is used to identify a significant difference at a significance level of 0.05 and 80% power (two-sample t-test).

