## Methods and analysis

### Objectives and study hypothesis

The objective of this trial is to compare the healing of the gluteus medius insertion among patients who have undergone THA. We will operate patients through the Hardinge approach and inject PRP or placebo in the region of the gluteus medius tendon insertion. The primary objective is to investigate the healing of the gluteus medius insertion objectively with MRI (anatomy) and hip strength measurements (dynamometer). The secondary objective is to record and analyze the changes in the Oxford Hip Score (OHS) by comparing the OHS before and after surgery and to record and analyze clinical signs, especially limping, pain and movement restrictions. The tertiary objective is to analyze safety and the cost-effectiveness of PRP in THA. The hypothesis is that PRP facilitates postoperative healing of the gluteus medius among elderly patients after THA and that the healing can be verified objectively seen by MRI and dynamometry.

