### Outcome measures

To measure objectively the healing of the gluteus medius and to check the positions of the components of the joint prosthesis, MRI and plain radiographs will be taken 3 and 12 months postoperatively. At the same control visits, a trained physiotherapist will measure the hip strengths and the OHS will be recorded. Clinical examinations will be conducted (movements of both hip joints, wound healing) and any limping or a positive Trendelenburg sign will be recorded.

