### Oxford hip score

Patients will fill OHS forms preoperatively and postoperatively at 3 and 12 months after surgery.

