### *Single* versus *multiple surgeons/centers*

Although single-center studies in RCTs has been met with criticism (Moseley et al. 2002), one of the main purposes of the pilot study protocol was to generate a logistically feasible setting which could be easily transferred to any other primary, secondary or tertiary hospital in Finland. As we want to know only the healing of the gluteus medius, objective methods of follow-up (MRI and strength assessment) will be used.

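### The Oxford Hip Score is the powered primary outcome in the sample size section but a secondary objective in the objectives section, so the only power statement does not cover the stated primary objective

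*Protocol article*

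**What the plan says.** Two sections of the protocol article assign the primary role differently.

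- *Data management and statistical analysis (sample size)* gives that role to the OHS: "Due to multiple outcome settings, the OHS was used as the primary outcome measure and power calculations were carried out accordingly". The calculation is for a two-sample t-test with a 5-point mean difference, SD 7.8, level 0.05 and 80% power, and gives 40 per group.
- *Objectives and study hypothesis*: "The primary objective is to investigate the healing of the gluteus medius insertion objectively with MRI (anatomy) and hip strength measurements (dynamometer"). The same paragraph continues: "The secondary objective is to record and analyze the changes in the Oxford Hip Score (OHS) by comparing the OHS before and after surgery". The hypothesis is that PRP aids healing of the gluteus medius and that "the healing can be verified objectively seen by MRI and dynamometry". It does not mention the OHS.

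On timing, *Oxford hip score* says "Patients will fill OHS forms preoperatively and postoperatively at 3 and 12 months after surgery", and *Outcome measures* says "MRI and plain radiographs will be taken 3 and 12 months postoperatively", with strength measured at the same visits. No section names 3 or 12 months as the primary time. The sample size section does not attach the 5 points to either time, or say whether they refer to the score or to its change from baseline.

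**The concern.** The primary endpoint decides what the trial may conclude and which comparison the sample size must support. Here the two disagree, with three consequences.

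First, a reader who takes the objectives section at its word finds a primary objective with no power statement: no effect size or SD is given for MRI or for strength.

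Second, a split result has no agreed meaning. Suppose strength (and MRI, if both are required) favours PRP and the OHS shows nothing. The objectives section would call the trial positive and the sample size section would call it negative. The pilot shows that such a split is conceivable, although with only 6 patients per arm. Maximum abduction strength rose by 39.1% with PRP against 6.2% with placebo, while the OHS gains differed by 23.5 − 20.2 = 3.3 points, less than the planned 5.

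Third, even if the OHS is accepted as primary, two postoperative OHS comparisons remain open while the calculation covers one.

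**Working it through.** **1. The plan's own figure.** Inputs from the sample size section: difference 5, SD 7.8, level 0.05, power 80%. Allocation is 1:1 (*Study design*). Sidedness is not stated; two-sided is assumed.

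n per group = 2 × (1.960 + 0.842)² × 7.8² / 5² = 2 × 7.85 × 60.84 / 25 = 38.2, so 39 by the normal formula. The exact t calculation gives 39.2, so **40**, as stated. A one-sided test would need only 2 × (1.645 + 0.842)² × 60.84 / 25 ≈ 30.1, so 31, which supports the two-sided reading.

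Power at 40 per group: the standard error is 7.8 × √(2/40) = 1.744, and 5 / 1.744 = 2.867. The normal approximation gives Φ(2.867 − 1.960) = 81.8%; the t-test gives 80.8%. The arithmetic is sound for **one** OHS comparison.

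**2. What that figure covers.**

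| Outcome | Rank in objectives section | Rank in sample size section | Power stated |
|---|---|---|---|
| MRI healing | primary | not ranked | none |
| Hip strength | primary | not ranked | none |
| OHS | secondary | primary | 80%, one test, time not given |

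No outcome is primary in both sections.

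**3. OHS at both times, each at 0.05.** If the tests are independent, 1 − 0.95² = 9.75%. Simulation of correlated normal statistics (1,000,000 draws) gives 9.1% at correlation 0.5 and 7.8% at 0.8. If both times were kept as primary with a Bonferroni split (0.025 each), power at 40 per group would be 71.9%, and 48 per group would be needed for 80%.

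**4. All three outcomes as alternative primaries at both times (six tests).** This is a conditional case that the document does not state.

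| Correlation (assumed) | At least one false positive, two-sided | At least one in favour of PRP |
|---|---|---|
| 0 | 1 − 0.95⁶ = 26.5% | 1 − 0.975⁶ = 14.1% |
| 0.5 | 20.7% | 10.4% |
| 0.8 | 13.8% | 6.9% |

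The right-hand column should be compared with a nominal 2.5%. It is the relevant one for a claim of benefit. The article gives no correlations, and some correlation is to be expected because all measures come from the same patients.

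**The case against.** The strongest reply is that the sample size section already deals with multiplicity: its opening words recognise several outcomes and answer by choosing one. On that reading at most two OHS tests remain open. This stands, and it limits the size of the error-rate concern. It does not resolve the conflict, because the objectives section ranks the OHS itself as secondary. The usual distinction between an objective and an outcome measure therefore does not help.

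A second reply is that this is a condensed article, and that the time point, testing order and multiplicity rule may be in a full protocol or analysis plan that is not shown. This also stands: their absence alone would be no finding. An unseen plan could not, however, make the two published rankings agree.

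A reader might go further and infer that the trial can declare success on any of six tests, with a 26% chance of a false claim. The documents do not support this. No section says that one positive test suffices. The objectives section joins MRI and strength with *and*; if both must succeed, error is not inflated across those two. The 26% also assumes independence and counts results that favour placebo.

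A reader might also cite "As we want to know only the healing of the gluteus medius, objective methods of follow-up (MRI and strength assessment) will be used" as a third conflicting ranking. That sentence stands under *Single versus multiple surgeons/centers* and explains the use of objective follow-up. It does not rank endpoints.

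Nor do the documents fix 3 months as the primary time. The pilot OHS is reported at 3 months without designating it, and its 3.3-point difference would give only about 46% power at SD 7.8 and 40 per group. The weakness figures in the Background, up to 85% and up to 10%, are for 6 months and 2 years and do not concern the OHS.

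**Conclusion.** The contradiction is real and is in the text shown. The OHS is primary where the trial is sized and secondary where its objectives are set. The 40 per group is right for one two-sided OHS test and says nothing about the power of the stated primary objective. A split result could be read either way.

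The time point is a smaller, related gap. Testing the OHS at both visits at 0.05 would give a false-positive rate of about 8% to 10%, for assumed correlations from 0.8 down to 0. If MRI and strength were also treated as alternative primaries, the rate would be about 14% to 26% two-sided, or about 7% to 14% in favour of PRP against 2.5%. Those last figures show what is at stake if the ranking stays open; they do not describe a rule that the article adopts.

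This should be corrected, because it determines what the trial can conclude.

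**What to change.** Before unblinding, make *Objectives and study hypothesis* and *Data management and statistical analysis (sample size)* name the same single primary endpoint, at one time point and on one scale (score or change from baseline).

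- **If the OHS is primary**, 40 per group remains valid. The sponsor should choose 3 or 12 months, justify the choice, and tie the 5-point difference and SD 7.8 to that time and scale. Strength, MRI and the other OHS time then become secondary, in a stated testing order or labelled exploratory.
- **If healing is the intended primary**, name strength or MRI at one time point and replace the OHS power statement with one for that endpoint. For strength, also choose the test position, since *Hip strength measurements* lists both supine and side-lying. The article gives no effect size or SD from which this sample size could be worked out, so 40 per group may not be enough.

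The first route needs wording changes only and no new data. The second adds a new calculation and possibly more patients. Either way the sponsor gives up some freedom over which outcome carries the conclusion. After unblinding, any choice would look driven by the data.

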**Methods:**

The study will be a multicenter, double-blinded and randomized study enrolling 90 patients based on power calculations. The efficacy of perioperative PRP treatment will be assessed by subjective and objective outcome variables. The participants will be randomized (sealed envelope) into either a placebo (saline) or a PRP group (1:1). For subjective outcomes, the Oxford Hip Score (OHS) will be collected before surgery and 3 and 12 months after surgery. The objective measures are findings at magnetic resonance imaging and plain radiographs and recorded values of measured strength.

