### Study design

The study is a multicenter RCT with parallel study groups (1:1). The study design is double blinded where neither the orthopedic surgeon nor the patient know whether the patient receives PRP treatment or placebo. The flowchart of the study cohort is shown in Fig. 1 including enrollment, allocation, follow-up and analysis. After having provided written informed consent the patients are enrolled. They participate voluntary in the study, they may withdraw from the trial at any time and are not compelled to explain the reason for withdrawal.

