### Baseline

The primary OA diagnosis will be made by the orthopedic surgeon who assesses whether the patient benefits from THA. In support of this decision, the surgeon will have access to plain radiographs of the affected hip joint and information on the range of movements of the hip joint. Inclusion mandates that the patient has OA Kellgren-Lawrence grade 3–4. The strength of both hips at baseline will be assessed by a physiotherapist on the day of surgery and the baseline OHS will be calculated and recorded.

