## Pilot study results

Our pilot study results have been presented previously at the German Congress of Orthopaedics and Traumatology 2017 (DKOU 2017) (Puhakka et al. 2017). A total of 12 patients participated in the pilot study in the Satakunta Central Hospital, Finland. The OHS of these patients increased in 3 months by 23.5 points in the PRP group compared to an increase of 20.2 points in the group who got placebo. The PRP group had a higher average increase in the maximum strength abduction compared to those who got placebo (39.1 vs. 6.2%). These preliminary results were in line with the power analysis, where significant differences (*p* < 0.05) are expected with 40 patients per study groups. The basic charasteristics of the pilot study group are given in Table 2.

**Table 2 Tab2:** Basic characteristics of pilot study groups

Characteristic	PRP *n* = 6	Placebo *n* = 6
Age, mean (range)	66.5 (63–72)	70.3 (68–73)
Gender (M / F)	3 / 3	5 / 1
Height (cm)	175 (165–183)	170 (156–179)
Weight (kg)	81.4 (72–90)	78.0 (63–87)
BMI	26.4 (25.5–26.9)	27.1 (21.3–30.1)
Illnesses		
Type 2 DM, oral medication	1	1
High blood pressure medication	3	–
Coronary artery disease	–	1
Hypercholesterolemia	–	1
Platelet-rich plasma characteristics		
Number of cells per patient (×10^6^, mean, 9 ml)		
Red blood cells	0.11	–
Leukocytes	1.10	–
Platelets	60.0	
Concentrations (× 10^9^, mean)		–
Red blood cells	0.12	–
Leukocytes	1.21	–
Platelets	66.7	

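### Baseline OHS is collected for every patient but not used as a covariate in any OHS analysis the article describes; adjusting for it is a near-free gain in precision

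*Protocol article*

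**What the plan says.** **Sizing.** The section on data management and statistical analysis (sample size) makes OHS the primary outcome for the power calculation. It assumes "a 5 point mean difference (SD 7.8 point") and states that "a sample size of 40 patients per intervention group has been calculated as being sufficient", "at a significance level of 0.05 and 80% power (two-sample t-test"). No other test is named anywhere in the article. The abstract gives the total as "enrolling 90 patients based on power calculations", that is, 45 per arm.

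**Objective.** Under Objectives and study hypothesis, the OHS aim is to "analyze the changes in the Oxford Hip Score (OHS) by comparing the OHS before and after surgery".

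**Pilot.** Under Pilot study results, the arms are compared on raw OHS change at 3 months (23.5 points on PRP, 20.2 on placebo). Strength is compared on percentage change: "The PRP group had a higher average increase in the maximum strength abduction compared to those who got placebo (39.1 vs. 6.2" percent).

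**Baseline data.** The Baseline section says that "the baseline OHS will be calculated and recorded" and that strength of both hips is measured on the day of surgery. The Oxford hip score section confirms a preoperative form and forms at 3 and 12 months.

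**The concern.** A pre-treatment measurement of the outcome can be ignored, subtracted, or used as a covariate. The article shows the first (the sizing test) and the second (the objective and the pilot). The third is the most efficient, needs nothing that is not already collected, and is not mentioned.

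Subtracting the baseline has a specific weakness. It assumes that each extra point at baseline carries through as a full extra point at follow-up. If the correlation is modest, subtraction adds noise: with equal SDs at the two visits, a change-score comparison is less precise than ignoring baseline altogether whenever r is below 0.5.

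The article also does not say whether 7.8 is the SD of the follow-up score or of the change. The power of the change comparison that the objective and pilot point to is therefore not determined by the design inputs. At stake is precision in a trial sized with almost no margin at 40 per arm.

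**Working it through.** **Inputs from the article:** difference 5, SD 7.8, alpha 0.05, power 80%, 40 per arm, 90 enrolled 1:1. **Assumed:** two-sided test (a one-sided test would need 31 per arm, which does not match); r, shown over a range; equal SDs at baseline and follow-up.

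**1. The article's own figure.** Normal approximation: n = 2 × (1.960 + 0.842)² × 7.8² / 5² = 38.2, so 39. The exact t calculation gives 39.2, so 40. At 40 per arm the noncentrality is 5 / (7.8 × √(2/40)) = 2.867 on 78 df, power 80.8%. At 45 per arm, power is 85.3%. The stated 40 is reproduced.

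**2. Why adjustment is never materially worse.** Each method compares the arms on Y − bX, where Y is follow-up and X is baseline OHS. Ignoring baseline sets b = 0 and change sets b = 1. The linear model estimates the b that minimises the variance, at the price of one degree of freedom and a variance factor of 1 + 1/(N − 4), here 1 + 1/76.

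**3. If 7.8 is the follow-up SD.**
- Adjusted SD = 7.8 × √(1 − r²), multiplied by √(1 + 1/76).
- Change SD = 7.8 × √(2(1 − r)).

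Example, r = 0.3. Adjusted: 7.44 × 1.0066 = 7.49, noncentrality 5 / (7.49 × 0.2236) = 2.99 on 77 df, power 83.8%. Change: SD 9.23, noncentrality 2.42 on 78 df, power 66.7%.

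Power at 40 per arm, against 80.8% unadjusted:

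| r | Baseline-adjusted | Raw change |
|---|---|---|
| 0 | 80.3% | 51.7% |
| 0.1 | 80.7% | 56.0% |
| 0.2 | 81.9% | 61.0% |
| 0.3 | 83.8% | 66.7% |
| 0.5 | 90.1% | 80.8% |
| 0.7 | 97.6% | 95.5% |

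**4. If 7.8 is the SD of the change.** The single-visit SD is 7.8 / √(2(1 − r)), so the adjusted SD is 7.8 × √((1 + r)/2): 6.29, 6.75 and 7.19 at r = 0.3, 0.5 and 0.7. The change test has 80.8% whatever r is. The adjusted model has 94.0%, 90.5% and 86.7%, or 93.7%, 90.1% and 86.2% with the small-sample factor.

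**5. Cost of adjusting.** Under the follow-up-SD reading the worst case is r = 0: 80.8 − 80.3 = 0.5 percentage points.

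**The case against.** The strongest reply is that the article fixes no final analysis. The t-test appears once, to justify the sample size, under a heading that itself refers to sample size. A full protocol or analysis plan may already contain an adjusted model, and a condensed article need not. Sizing on an unadjusted test and then adjusting is legitimate, and conservative if 7.8 is the follow-up SD. All of this stands, and it is why the point is an improvement and not an error.

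A reader might infer more in several places, and the article does not support it:

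- *That the t-test is the planned final analysis.* It is given only as the basis of the sample size.
- *That the OHS objective is a before-after comparison that cannot show a PRP effect.* Taken alone, the wording allows this. But the design section says "The study is a multicenter RCT with parallel study groups (1:1"), the sizing uses a two-sample test, and the pilot compares changes between arms. The changes evidently feed a between-arm comparison.
- *That percentage change is the trial's strength endpoint.* It appears only as a pilot summary; the hip strength section names no such endpoint.
- *That the pilot's age and sex differences call for this adjustment.* Six per arm says little about 40 or more, adjusting for baseline OHS does not directly correct age or sex imbalance, and chance imbalance does not invalidate an unadjusted randomised comparison.
- *That change scores will leave the trial underpowered.* That follows only if 7.8 is the follow-up SD and r is below about 0.5. If 7.8 is the SD of change, the change test keeps its 81%.

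The size of the gain also rests on an unknown r, and at low r it is negligible.

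**Conclusion.** The point holds as an efficiency improvement. The sample size is correct for its inputs, and nothing described is invalid. If 7.8 is the follow-up SD, adjusting gains nothing to about 1 point over the unadjusted test at r = 0.1–0.2, about 3 points at 0.3, 9 at 0.5 and 17 at 0.7. Over raw change scores it gains about 17 points at r = 0.3, 9 at 0.5 and 2 at 0.7. If 7.8 is the SD of change, it gains roughly 13, 9 and 5 points at those three values. These figures assume a two-sided test, equal SDs at the two visits and a value of r that the article does not supply. The direction does not depend on r, apart from the loss of about half a point at worst. The ambiguity over what 7.8 measures is in the text itself and should be resolved whichever model is used.

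**What to change.** State the following in the analysis section, before unblinding:

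1. The primary OHS analysis is a between-arm linear model of follow-up OHS on treatment and baseline OHS, reported as an adjusted mean difference with 95% CI. The unadjusted comparison is supportive.
2. Operated-side abduction strength is analysed the same way, in absolute units with its own baseline as covariate.
3. SD 7.8 is identified as that of the follow-up score or of the change.

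Reword the OHS objective as a difference between arms so that it matches. If an existing analysis plan already specifies such a model, only the objective and the SD need aligning.

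The cost is about one paragraph. No new data, visits or patients are needed, and the 40 per arm can stay.

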### Ethics

The etics committee of the Hospital District of Southwest Finland approved the study (ETMK 77/2015, 21.3.2017).

### *Single* versus *multiple surgeons/centers*

Although single-center studies in RCTs has been met with criticism (Moseley et al. 2002), one of the main purposes of the pilot study protocol was to generate a logistically feasible setting which could be easily transferred to any other primary, secondary or tertiary hospital in Finland. As we want to know only the healing of the gluteus medius, objective methods of follow-up (MRI and strength assessment) will be used.

## Pilot study results

Our pilot study results have been presented previously at the German Congress of Orthopaedics and Traumatology 2017 (DKOU 2017) (Puhakka et al. 2017). A total of 12 patients participated in the pilot study in the Satakunta Central Hospital, Finland. The OHS of these patients increased in 3 months by 23.5 points in the PRP group compared to an increase of 20.2 points in the group who got placebo. The PRP group had a higher average increase in the maximum strength abduction compared to those who got placebo (39.1 vs. 6.2%). These preliminary results were in line with the power analysis, where significant differences (*p* < 0.05) are expected with 40 patients per study groups. The basic charasteristics of the pilot study group are given in Table 2.

**Table 2 Tab2:** Basic characteristics of pilot study groups

Characteristic	PRP *n* = 6	Placebo *n* = 6
Age, mean (range)	66.5 (63–72)	70.3 (68–73)
Gender (M / F)	3 / 3	5 / 1
Height (cm)	175 (165–183)	170 (156–179)
Weight (kg)	81.4 (72–90)	78.0 (63–87)
BMI	26.4 (25.5–26.9)	27.1 (21.3–30.1)
Illnesses		
Type 2 DM, oral medication	1	1
High blood pressure medication	3	–
Coronary artery disease	–	1
Hypercholesterolemia	–	1
Platelet-rich plasma characteristics		
Number of cells per patient (×10^6^, mean, 9 ml)		
Red blood cells	0.11	–
Leukocytes	1.10	–
Platelets	60.0	
Concentrations (× 10^9^, mean)		–
Red blood cells	0.12	–
Leukocytes	1.21	–
Platelets	66.7	

